#### Secondary outcomes

2.8.2

National Institute of Health Stroke Scale (NIHSS)^[20]^ scores for neurological deficit, Modified Barthel Index (MBI)^[21]^ scores for activities of daily living, Brunnstrom stroke recovery Scale^[22]^ scores for limb muscle strength, stroke Chinese medicine symptom Scale^[23]^ scores for curative effects of stroke. These scales will be used to evaluate efficacy at before and the 0 hour, 24 hours, 36 hours after treatment, and 1 week follow-up period. Participants’ diary for their temperature, breathe, heart rate, blood pressure, drugs, adverse events (AE), and others during the research was recorded. All the dropouts and causes will be documented in case report form (CRF). The study schedule is shown in Figure 3.

**Figure 3 F3:**
[figure not shown]
SPIRIT figure.

### Adverse events

2.9

Any possible AE related to acupuncture intervention that occur, including nausea, subcutaneous bleeding or hematoma, needle stuck or breakage, and pain will be checked and treated. Details of AE will be recorded in the CRF by the acupuncturist and security administrator. Severe AE will be reported to the Ethics Committee. Participants who are unwilling to persist with the treatment will be removed from the trial.

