**Design::**

This is a multicenter, central-randomized, controlled, double-blind, noninferiority, 2 factors and 3 levels orthogonal clinical trial. A total of 100 participants with ischemic stroke aged from 40 to 80 were randomized into experimental group and control group, the experimental group was divided into 9 groups (A1-A9) according to different factors or levels, and each group have 10 participants. The whole study period is 17 days, including 1 week for baseline observation, 3 days treatment and observation, and 1 week follow-up. Primary outcome is the fMRI based on blood oxygenation level dependent. Secondary outcomes included National Institute of Health Stroke Scale, Modified Barthel Index, Brunnstrom stroke recovery, stroke Chinese medicine symptom. Clinical assessments will be evaluated at before and the 0 hour, 24 hours, 36 hours after treatment, and 1 week follow-up. The primary outcome of the postacupuncture effect were investigated by paired T-test, and the continuous outcome variables will be analyzed with univariate repetitive measurement deviation analysis. Adverse events will be noted and recorded for the safety evaluation.

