#### Inclusion criteria

2.5.1

The inclusion criteria contain the following items:

1.Subjects diagnosed with ischemic stroke in International Classification of Diseases (ICD-10-I63.902)^[18]^;2.Subjects diagnosed ischemic stroke for the first time, and the onset time is not more than 3 months;3.Subjects aged between 40 and 80 years old, male or female;4.Conscious, no dementia, normal communication and cooperation during examination;5.Right-handed.

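### Section 2.9 frames adverse events by possible relation to acupuncture while the Abstract and section 2.8.2 do not, so events put down to the stroke or the scan may be missing from the CRF safety set

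*Protocol article*

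**What the plan says.** Section 2.9 (Adverse events) of the protocol article is the only section on handling adverse events. Its first sentence reads "Any possible AE related to acupuncture intervention that occur, including nausea, subcutaneous bleeding or hematoma, needle stuck or breakage, and pain will be checked", and it goes on to say that these events will also be treated. Every example it gives is a reaction to needling. The next sentence is "Details of AE will be recorded in the CRF by the acupuncturist and security administrator", followed by "Severe AE will be reported to the Ethics Committee". Neither of these repeats the link to acupuncture.

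Two other places mention adverse events with no such link. The Abstract (Design) says "Adverse events will be noted and recorded for the safety evaluation". Section 2.8.2 (Secondary outcomes) lists what the participants' diary holds, ending with "drugs, adverse events (AE), and others during the research was recorded". Section 2.8.2 sends dropouts and their causes to the CRF. It does not say that diary events go there, and neither does any other section.

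The population is set in section 2.5.1: "Subjects diagnosed ischemic stroke for the first time, and the onset time is not more than 3 months". No minimum time since onset is given. Section 2.8.1 schedules one MRI before treatment and three after it, at 0, 24 and 36 hours.

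**The concern.** In a single patient it is seldom possible to tell whether an event was caused by the treatment. The sounder evidence is the randomised comparison of all events, whatever anyone thought caused them. If possible relation to acupuncture decides what enters the CRF, part of that comparison is settled by opinion before the data are collected.

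Two features of this trial make that more than a formality. Participants are within 3 months of a first stroke, so neurological events are plausible and easily put down to the disease. One of the two CRF recorders is the acupuncturist, who performs the manipulation and so must know what was given. A relatedness filter in that person's hands can work differently in the two arms even when the written rule is the same. The arms also use different acupoints (sections 2.7.1 and 2.7.2), so the reactions a recorder expects may differ.

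At stake are the completeness and fairness of the safety summary. The fMRI primary outcome is not affected.

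**Working it through.** The article gives no adverse event rate and no safety figure to reproduce, so the check is mainly a reading of the text.

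**Step 1: scope in each place.**
- Abstract: adverse events, no limit.
- Section 2.8.2, diary: adverse events during the research, no limit.
- Section 2.9, first sentence: events possibly related to acupuncture.
- Section 2.9, CRF sentence: no scope of its own. Its nearest antecedent is the set just described, so the natural reading carries the limit forward.

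Two centres following the text in good faith could therefore build different safety datasets.

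**Step 2: where each kind of event would be captured.**

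| Event | Route in the article | Certain to reach the CRF as an adverse event? |
|---|---|---|
| Needling reaction | Section 2.9 | Yes |
| Severe event of other cause | Ethics Committee report (2.9); dropout cause in the CRF if it is a severe change during treatment (2.5.3, 2.8.2) | Depends on the reading of 2.9 |
| Non-severe neurological worsening | NIHSS at 0, 24 and 36 hours and 1 week; diary (2.8.2) | Not stated; the NIHSS gives a score, not an event record |
| Blood-pressure event | Diary (2.8.2) | Not stated |
| Fall, or intolerance of the scan | Diary (2.8.2) | Not stated |

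The dropout route is narrow. Section 2.5.3 refers to severe changes during treatment, and section 2.7.1 says acupuncture is given once, so events in the follow-up week arguably fall outside it.

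**Step 3: how much a comparison by arm could show at best.** Inputs are 100 participants (section 2.1) and 9:1 allocation (section 2.6). That gives 9 × 10 = 90 experimental and 10 control participants; 90 + 10 = 100 agrees with the stated total.

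Exact one-sided 95% upper limit when no event is seen: 1 − 0.05^(1/n).
- n = 10: 1 − 0.05^(1/10) = 25.9%
- n = 90: 1 − 0.05^(1/90) = 3.3%

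Chance of seeing at least one event: 1 − (1 − p)^n, with p an assumed true rate.

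| Assumed p | 10 controls | 90 experimental |
|---|---|---|
| 1% | 9.6% | 59.5% |
| 2% | 18.3% | 83.8% |
| 5% | 40.1% | 99.0% |
| 10% | 65.1% | >99.9% |

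Even with complete recording, the control arm says little about uncommon events. With so few controls, one missed event there changes the observed rate by 1/10 = 10 percentage points.

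**The case against.** The best reply is grammatical. In section 2.9 the words "Any possible AE related to acupuncture intervention that occur" are the subject of a care provision, which ends "needle stuck or breakage, and pain will be checked and treated". Recording is covered by the next sentence, which carries no relatedness condition, and the sentence on severe events carries none either. The word for possible relation does not describe a completed causal judgement, and the list of examples is not exhaustive. The diary, the scheduled NIHSS, the dropout causes and the Ethics Committee report all give further capture. One written rule covers both arms. Finally, this is a condensed article, and the full protocol or the CRF may already define these things.

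Much of this stands. It rules out a stronger reading that a reader might infer: that only events already judged related are recorded, that recurrent stroke and other serious events go uncounted, and that the arms therefore cannot be compared on safety. The documents do not say that, and the routes above contradict it in part. Nor can a percentage of lost events be given, since any such figure would merely restate an assumed share of unrelated events.

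The inconsistency itself remains. The scope in section 2.9 is stated and is not simply left to a fuller document. It differs from the other two places, and the other routes do not put non-severe events into the CRF as adverse events. The same written rule does not guarantee the same application when one of those applying it knows the treatment.

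**Conclusion.** The point holds as a conflict of scope that should be reconciled. On its natural reading, section 2.9 limits the CRF set to possibly acupuncture-related events, whereas the Abstract and section 2.8.2 set no limit and no text links the diary to the CRF. The safety summary by arm may therefore be incomplete, and it may be biased in a direction that cannot be predicted. The size of the loss is unknown because no event rate is given. Precision is poor regardless, with an upper limit of 25.9% on zero events among 10 controls against 3.3% among 90 experimental participants. That small arm is a separate limitation and no reason to accept incomplete records.

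The conclusion rests on two assumptions: that the CRF sentence refers back to the events named just before it, and that the acupuncturist knows the allocation, which follows from the task of delivering it. If the full protocol already requires all-cause recording, only the article's wording needs correcting.

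**What to change.** Reconcile section 2.9 with the Abstract and section 2.8.2. Suggested content for 2.9:

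> All adverse events from needle insertion to the 1-week follow-up, including every event entered in the participant's diary, are recorded in the CRF whatever their presumed cause. This includes neurological worsening and events during MRI. Possible relation to acupuncture is rated in a separate CRF field. All-cause events are reported by randomised arm, with possibly related events as a subset.

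The needling reactions now listed can stay as examples. Where feasible, relatedness is better rated by someone who does not know the allocation.

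The cost is a change of wording, one CRF field, a few more events to enter, and a reported adverse event rate that will look somewhat higher. The change needs no new visits.

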### Statistical analysis

2.10

The BOLD-fMRI data processing and analysis is based on the DPABI 4.3 of Matalab platform. Including removal of the first 10 time points, time correction, head movement correction (eliminating the data of head movement translation >2 mm or rotation shift >2°). Regression white matter and cerebrospinal fluid signals were used to remove interference. Spatial normalization, spatial smoothing, and linear drift removal were performed. If the data met normal distribution, the image characteristics of the postacupuncture effect were investigated by paired T-test.

Firstly, a gray matter mask was made for the subjects in this study, and the differences before acupuncture were found by paired T-test (*P* < .05). The whole brain gray matter mask was used to subtract the areas with significant differences before acupuncture, so as to exclude the pixels with significant differences at baseline. Paired T-test was used to investigate the changes of fALFF, ReHo, DC, and seed point FC before and after acupuncture in the intra-group comparison. Paired T-test was used to further find the differences in cerebral activity between groups compared with different stimulation quantity. The statistical results were corrected, if the threshold voxel level *P* < .01 and the cluster level *P* < .05, the difference was statistical significance.

Continuous outcome variables including NIHSS scores, MBI scores, Brunnstrom scores and stroke Chinese medicine symptom scores at before and the 0 hour, 24 hours, 36 hours after treatment, and 1 week follow-up will be analyzed with univariate repetitive measurement deviation analysis. Chi-Squared test will be used for comparison between groups.

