### Study design

2.1

This is a multicenter, central-randomized, controlled, double-blind, noninferiority, 2 factors and 3 levels orthogonal trial. A total of 100 participants were randomized into experimental group and control group, the experimental group was divided into 9 groups (A1-A9) according to different factors or levels, and each group have 10 participants. This trial recruited participants from 3 sub centers: the First Affiliated Hospital of Yunnan University of Traditional Chinese Medicine (TCM), the Affiliated Hospital of Yunnan University and Kunming Yan’an Hospital, recruitment advertisements will be placed on the network and bulletin boards. Eligible participants will have an equal chance of being allocated randomly to experimental group or control group.

The whole study period is 17 days, including 1 week for baseline observation, 3 days treatment and observation, and 1 week follow-up. Participants will be monitored cerebral functional connectivity changes by fMRI before and the 0 hour, 24 hours, 36 hours after treatment, and scales was used to evaluate the clinical efficacy during the treatment and follow-up period. Figure 1 shows a flowchart of the study.

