### Randomization, allocation concealment, and blinding

2.6

After recruitment, a statistician who is not taking part in the clinical intervention will use SPSS 25.0 (IBM, Chicago, IL) to generate a random allocation sequence, the eligible participants who meet the inclusion criteria will be randomly distributed to experimental group and control group with proportion of 9:1. Participants in the experimental group will random reassignment to A1-A9 via the central randomization system by statistician from each sub centers. Each subject will received a unique random ID. The allocation concealment procedure will not be exposed until the clinical trial is finished completely. The baseline assessment and questionnaire administration was conducted by researcher A. Assessments and measurements of the participants will be carried out before and after the treatments by researcher B. Researcher C as image analyst will processed and analyzed the fMRI images to observed the cerebral functional connectivity changes. A licensed acupuncture researcher who has worked for more than 10 years will conduct acupuncture intervention on participants, whereas all subjects will deprived from knowing something about the pattern of treatment.

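### Removing voxels that differ at baseline (P < .05) from the grey-matter mask discards brain by chance, makes search regions non-comparable, and leaves most baseline imbalance in place

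*Protocol article*

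**What the plan says.** Section 2.10 of the protocol article sets out the order of the voxel-wise analysis of the primary outcome. A grey-matter mask is made first. Then "the differences before acupuncture were found by paired T-test (*P* < .05"; no correction is mentioned at this point. The significant areas are taken out of the mask: "The whole brain gray matter mask was used to subtract the areas with significant differences before acupuncture", with the stated aim "so as to exclude the pixels with significant differences at baseline". The maps of fALFF, ReHo, DC and seed-point FC are compared only after that, first within groups and then between them: "Paired T-test was used to further find the differences in cerebral activity between groups compared with different stimulation quantity". Correction comes last: "if the threshold voxel level *P* < .01 and the cluster level *P* < .05, the difference was statistical significance".

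On design, section 2.1 says "A total of 100 participants were randomized into experimental group and control group" and "the experimental group was divided into 9 groups (A1-A9) according to different factors or levels, and each group have 10 participants". Section 2.6 says participants are "randomly distributed to experimental group and control group with proportion of 9:1", with a second random assignment to A1-A9.

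**The concern.** The baseline sentence does not say that the test is between groups. Before the single acupuncture session, though, no other contrast fits the stated aim. Under randomisation, a between-arm difference at that point is chance. Testing for it and deleting what is significant has three consequences.

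- Voxels leave the analysis for a reason unrelated to treatment, and they may lie in regions where an effect is expected.
- If each comparison has its own mask, a region can be testable in one contrast and absent from another. Section 3 wants to learn which of time and frequency matters most and which combination is best, and that needs contrasts over the same brain.
- A significance filter removes only the largest gaps. With 10 per arm, most of the imbalance the step is meant to deal with passes through.

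**Working it through.** The article gives no sample-size calculation or effect size, so there is no such figure to reproduce. Its arithmetic is consistent: 10 groups × 10 = 100, and a 9:1 split gives 90 and 10.

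**Inputs.** From the article: 10 per arm, 10 arms, baseline threshold P < .05 (sections 2.1 and 2.10). Assumed: two-sided tests, normal data with SD 1, complete data, the same baseline distribution in every arm (which randomisation implies), and a pre-post correlation r from 0.3 to 0.9, because the article gives none. The article names a paired test even between independent groups. That is a separate matter, so both forms were run.

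**1. Voxels lost by chance.** One two-arm test removes 5% of null voxels by construction (simulated: 4.95% independent-samples, 5.00% paired). For a common mask that drops any voxel significant in any comparison, the simulated loss is:

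| Comparisons feeding one common mask | Number | Independent-samples test | Paired test |
|---|---|---|---|
| Nine arms against control | 9 | about 27% | about 28-29% |
| All pairs of A1-A9 | 9×8/2 = 36 | about 57% | about 63% |
| All pairs of ten arms | 10×9/2 = 45 | about 63% | about 70% |

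These are expected shares. Spatial correlation between voxels makes the loss patchy but does not change the expectation.

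**2. Gap needed to flag a voxel.** Critical difference = t(0.975, 18 df) × SD × √(2/10) = 2.101 × 1 × 0.447 = 0.94 SD. A true gap of 0.5 SD is flagged 19% of the time and one of 0.8 SD 40% of the time (noncentral t, 18 df).

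**3. Imbalance left behind.** Before masking, the variance of the baseline gap is 2/10 = 0.20 (SD 0.447). In the voxels retained after the independent-samples test the SD is about 0.396, so the variance is about 0.157, and 0.157/0.20 = 0.78. With the paired test the retained share is about 0.81. About 81% of voxels with an observed gap above 0.5 SD stay in.

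**4. Effect on the later between-arm test.** Null simulation in retained voxels, independent-samples test at nominal .01, r from 0.3 to 0.9:

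- post-treatment values: 0.0091 falling to 0.0015;
- change scores: 0.0074 rising to 0.0096.

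Neither is above .01. Selecting on pre-treatment data makes the later test conservative.

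**5. What baseline adjustment would give.** Variance relative to an unadjusted post-treatment comparison is 1 − r² for ANCOVA and 2(1 − r) for change scores:

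| Assumed r | ANCOVA | Post-only | Change score |
|---|---|---|---|
| 0.3 | 0.91 | 1 | 1.4 |
| 0.5 | 0.75 | 1 | 1.0 |
| 0.7 | 0.51 | 1 | 0.6 |
| 0.9 | 0.19 | 1 | 0.2 |

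These formulas ignore the cost of estimating the slope. With only two arms of 10 in the model, the simulated variance of the arm difference in retained voxels under masking (post-treatment values), against ANCOVA over all voxels, is 0.197 v 0.194 (r = 0.3), 0.190 v 0.160 (0.5), 0.179 v 0.108 (0.7) and 0.165 v 0.040 (0.9). The gain is negligible at r = 0.3 and clear from 0.5 upward.

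**The case against.** Four points can be made for the plan or against a harsher criticism of it.

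*False positives.* A reader might infer that the remaining imbalance, or regression to the mean, would show up as an acupuncture effect, or that a data-selected search volume inflates error. The plan does not support this. In a randomised comparison, chance imbalance is already in the standard error, and the mask is chosen from pre-treatment data only. Step 4 shows no inflation. This objection stands in full.

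*Size of the loss.* A reader might infer that most of the brain is deleted. That needs one common mask built from every pairwise test, and the article does not say so. The text is compatible with anything from about 5% per contrast to about 70%. This stands as a limit on the claim. It does not rescue the step, because at the 5% end the search region changes from contrast to contrast.

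*Baseline adjustment.* A reader might infer that the between-group test ignores baseline. The preceding sentence concerns before-to-after changes, so a change-score contrast is a fair reading, and a covariate may be specified in a fuller document. The text does not settle this, so its silence is not counted as an error. Only the masking, which is stated, is at issue.

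*Correction at baseline.* The cluster correction might also cover the baseline step. Chance deletion would then be much smaller, but more imbalance would stay. The text gives only P < .05 for that step.

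**Conclusion.** The point holds in limited form. Section 2.10 fixes a step that is unnecessary in a randomised trial and fails its own aim. It removes about 5% of null voxels per two-arm comparison, flags only gaps of about 0.94 SD or more, and leaves about 78% of the baseline-gap variance in the retained voxels. The cost is lost coverage, search regions that may not match across contrasts, and precision forgone compared with baseline adjustment. Type I error is not the problem.

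The 5% and 78% figures rest on 10 per arm, normality and an uncorrected P < .05. The larger losses (27-70%) also need a common mask, which the article leaves open. The precision gain depends on an r that the article does not give. The step should be corrected before the images are analysed, but it does not by itself invalidate the trial.

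**What to change.** Delete the sentences in section 2.10 that test for pre-acupuncture differences and subtract the significant areas. State instead that one fixed grey-matter mask is used for all participants, all four measures and all contrasts. In every between-arm model, enter each participant's baseline value at that voxel for the same measure (fALFF, ReHo, DC or FC) as a covariate.

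No new data are needed, because a scan before treatment is already planned for every participant (sections 2.1 and 2.8.1). The cost is one degree of freedom per model and slightly more analysis work. If r proves to be low, the covariate gains little, but the fixed mask still keeps full coverage and the same search region for every contrast.

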### Interventions

2.7

The intervention measures were selected according to the theory and experience of TCM. Both experimental group and control group received acupuncture treatment, but the prescription of acupoints was different. In addition, the use of conventional drugs in neurology department is allowed, such as antiplatelet drugs, antihypertensive drugs, lipid-regulating drugs, and drugs used will be documented in detail. This study used the same acupuncture instruments of disposable sterile needles (0.25 × 40 mm), acupoints location, and operation were carried out according to the National Standard of the People's Republic of China in 2006, Nomenclature and Location of Acupuncture Points (GB/T12346-2006).^[19]^

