#### Experimental group

2.7.1

The acupoint prescription was “Shenyang Tongdu” acupuncture according to TCM theory and clinical experience. Acupoints are including DU14 (Dazhui), DU9 (Zhiyang) and DU4 (Mingmen). The experimental group adopted 2 factors and 3 levels orthogonal trial, the 2 factors of time and frequency include 3 levels of different parameters, and the intersection of different parameters constituted 9 groups (A1-A9). Time refers to the operating time, including 60 seconds, 120 seconds, 180 seconds. Frequency refers to the twists per minute without lifting, including 120 bpm, 180 bpm, 240 bpm, the range of twirling manipulations is about 180°. Participants only received acupuncture once, and the rest of the time was observation and follow-up period. Specific parameters of each experimental group are shown in Figure 2.

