#### Control group

2.7.2

The control group was treated with “Xingnao Kaiqiao” acupuncture, this is a standard prescription for stroke treatment in China, which has been proved effective in large sample trials. Acupoints are including DU26 (shuigou), and hemiplegia side PC6 (neiguan), HT1 (jiquan), LU5 (chize), BL40 (weizhong), and SP6 (sanyinjiao). The operation method is carried out according to the prescription, and the operation time is 2 minutes for each point. Participants only received acupuncture once, and the rest of the time was observation and follow-up period.

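### The within-arm before/after test is read as the acupuncture effect, but every arm is needled, so it cannot separate acupuncture from other change

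*Protocol article*

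**What the plan says.** The abstract (Design) ties the primary outcome to one test: "The primary outcome of the postacupuncture effect were investigated by paired T-test". Section 2.10 (Statistical analysis) gives the detail for the imaging measures: "Paired T-test was used to investigate the changes of fALFF, ReHo, DC, and seed point FC before and after acupuncture in the intra-group comparison". The next sentence adds a second comparison: "Paired T-test was used to further find the differences in cerebral activity between groups compared with different stimulation quantity".

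Four other statements determine what a within-arm change can mean:

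- Section 2.5.1 (Inclusion criteria): "Subjects diagnosed ischemic stroke for the first time, and the onset time is not more than 3 months". No lower limit on time since onset is given.
- Section 2.7 (Interventions): "Both experimental group and control group received acupuncture treatment, but the prescription of acupoints was different". Section 2.7.2 makes the comparator active: "The control group was treated with “Xingnao Kaiqiao” acupuncture, this is a standard prescription for stroke treatment in China".
- Section 2.7 also says that "the use of conventional drugs in neurology department is allowed".
- Section 2.7.1: "Participants only received acupuncture once, and the rest of the time was observation and follow-up period". Under section 2.8.1, imaging is done before treatment and at 0, 24 and 36 hours after it. Section 2.8.2 carries the clinical scales on to 1 week.

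The article describes no sham or untreated arm and no second pre-treatment scan from which change without needling could be estimated.

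**The concern.** A paired test within one arm asks whether the mean moved between two scans. It does not ask why. Recovery after a recent stroke, changes in medication, habituation to the scanner and the non-specific experience of being needled all enter the same difference. Labelling that difference the post-acupuncture effect credits all of it to acupuncture.

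The analysis steps in section 2.10 do not remove the problem. Linear drift removal is listed among the image-processing steps and does not correct change from one session to the next. The baseline mask removes pixels that differ before acupuncture, not pixels that later change for other reasons. Section 2.8.1 treats agreement between imaging measures as raising credibility, but fALFF, ReHo, DC and FC all come from the same scans and share the same confounding.

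At stake is the mechanistic claim in the abstract and Discussion. A brain region could be reported as responding to acupuncture when the design cannot show that it would have stayed still without it.

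**Working it through.** The plan states no figure to reproduce here: the article gives no effect size, SD or power calculation. The check asks how often the within-arm test is significant when acupuncture does nothing, and whether the between-arm test has the same weakness.

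**Inputs**
- From the protocol: 10 patients per arm and ten arms (section 2.1); a paired t-test (section 2.10); a voxel threshold of 0.01 with a cluster threshold of 0.05 (section 2.10).
- Assumed: a drift of d SDs of the change score from causes other than acupuncture. The documents give no value, so a range is shown.

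**Step 1. Within-arm test, true acupuncture effect zero.** With n = 10 the statistic follows a noncentral t distribution with 9 degrees of freedom and noncentrality d × √10. The probability of significance is P(|T| > critical value), two-sided.

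| Drift d (SD of change) | Noncentrality d√10 | P(significant) at 0.05 | P(significant) at 0.01 |
|---|---|---|---|
| 0.1 | 0.32 | 0.059 | 0.013 |
| 0.3 | 0.95 | 0.136 | 0.037 |
| 0.5 | 1.58 | 0.293 | 0.103 |
| 0.8 | 2.53 | 0.616 | 0.310 |

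The 0.01 column is closer to the plan's voxel threshold. Both columns describe a single voxel or regional value. The rate after cluster correction depends on how far the change extends in space and cannot be computed from the documents.

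**Step 2. Between-arm test under the same drift.** If two arms of 10 both drift by 0.5 SD and acupuncture does nothing, a two-sample test of change scores rejects in 5.0% of simulated trials at 0.05 and 1.0% at 0.01. The common drift cancels.

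**Step 3. Chance imbalance in time since onset.** Assume onset-to-treatment time is uniform over 0 to 90 days. Its SD is 90/√12 = 26.0 days, and the difference between two arm means has SE 26.0 × √(2/10) = 11.6 days. Two arms differ by more than 14 days in 23% of simulated trials.

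To see whether this harms the between-arm test, let drift fall linearly from 2k SD at day 0 to zero at day 90, with no treatment effect. For k = 0.3, 0.5, 0.8 and 1.5, the two-sample test of change rejects in 5.1%, 4.9%, 5.0% and 5.0% of simulated trials at 0.05, and in about 1.0% at 0.01. The error rate holds.

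The cost is precision. Onset adds variance (2k)²/12 = k²/3 to a residual variance of 1, so it explains (k²/3)/(1 + k²/3) of the variance in change:
- k = 0.3: 0.030/1.030 = 3%
- k = 0.5: 0.083/1.083 = 8%
- k = 0.8: 0.213/1.213 = 18%

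**The case against.** The strongest reply is that this is a matter of wording. The stimulation-quantity question is about differences between randomised arms, and section 2.10 plans that comparison directly after the within-arm one. The control is active by choice in a trial declared as noninferiority. Imaging stops at 36 hours after a single session, so spontaneous change may be slight; at 0.1 SD the within-arm rejection rate is 5.9%, hardly above nominal.

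Much of this stands, and it rules out several stronger readings:

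- A reader might infer that the trial cannot tell whether connectivity change depends on stimulation quantity. The documents do not support that: the between-group contrast is planned, and randomisation protects it from common change. Its being named a paired test although the groups are independent is a separate point.
- A reader might infer that chance imbalance in time since onset would pass for a stimulation effect. Step 3 shows that it does not raise the false-positive rate.
- A reader might infer that natural recovery will be reported as a mechanism. The documents do not establish its size. It is probably small at 0 hours, and larger at 36 hours and for the 1-week scales.
- A reader might work out the false-positive rate for all 90 experimental patients together. The article plans no such pooled test.
- A reader might fault the article for naming no covariate or stratification factor. A condensed article may leave these to a fuller document.

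What the reply does not remove is the label. The abstract and section 2.10 attach the acupuncture effect to the within-arm test, and no analysis plan, seen or unseen, can supply an arm that was not needled.

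**Conclusion.** The point holds for the within-arm reading of the primary outcome and goes no further. As written, the plan credits acupuncture with any change between scans, and the design has no means of separating the two.

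The size is unknown. Under the assumed drifts of 0.1 to 0.8 SD, a within-arm test with no acupuncture effect is significant with probability 0.06 to 0.62 at 0.05, and 0.01 to 0.31 at 0.01. These rates assume normally distributed change scores and one measure at one location. The lower end may be the more realistic for the 0-hour scan. That recovery varies with time since onset is a general clinical premise that the documents do not quantify; the within-arm conclusion does not depend on it.

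The randomised comparison of stimulation quantity remains valid with respect to this concern.

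**What to change.** 1. In section 2.10 and the abstract, describe the within-arm before/after maps as change over time, and stop calling them the post-acupuncture effect.
2. Make the randomised difference in change, between arms or between levels of time and frequency, the basis for any conclusion on stimulation quantity. Adjust it for the patient's own pre-treatment value and, for precision, for days since onset, which has to be established for eligibility.
3. Limit the stated conclusion to differences between stimulation levels or between the two prescriptions. Say that, with every arm needled, change common to all arms cannot be attributed to acupuncture itself.

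No extra patients, scans or visits are needed. The cost is a less favourable claim for the within-arm results and a few degrees of freedom: two covariates take the error degrees of freedom from 20 − 2 = 18 to 16 in a comparison of two arms, or from 100 − 10 = 90 to 88 in a model with all ten arms.
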